**Statistical considerations**

Determination of sample size

The sample size calculation (G power software) was done in order to allow demonstrating a slight difference between the 2 countermeasures (coffee and blue light) with a power of 90 % and a type-I error =5% approximately 48 subjects have to be included in the study:

Effect size f = 0.3

α err prob = 0.05

Power (1-β err prob) = 0.9

Total sample size: 48 **(24 young and 24 middle-aged)**

**Analyses of variables**

Analysis of primary efficacy variable

The results will be analyzed by using negative binomial regres­sion in Stata, version 8.0 (Stata Corp., College Station, Texas), using number of ILC per participant as dependent variables and treatments (Blue light, coffee, or placebo), age or type as determi­nants clustered on participants. We reported comparisons of ILC between treatments as incidence rate ratios (IRR) with 95% confi­dence intervals (CI). Where binomial negative regression are not possible because there are no line crossing, the Wilcoxon non­parametric test will be used.

Analysis of secondary efficacy variables

The standard deviation of the position of the car will be compared by a two-way analysis of variance (ANOVA) (age*treatment, genotype*treatment, hormonal type *treatment, cognitive type*treatment, …).

Subjective sleepiness or subjective fatigue will be compared by a three-way analysis of variance for repeated measurements (rANOVA) (time*age*treatment, time*genotype*treatment, time*hormonal type*treatment, time*cognitive type*treatment, …)

Sleep latency, sleep efficiency or sleep EEG power density will be compared by a three-way analysis of variance for repeated measurements (rANOVA) (time*age*treatment, time*genotype*treatment, time*hormonal type*treatment, time*cognitive type*treatment, …).

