**Study objectives**

Primary objective

To compare the effects of continuous blue light exposure during driving with those of coffee (2*200 mg of caffeine) and coffee placebo on 4h night-time driving performance in young (20-25 years) and middle-aged (40-50 years) healthy volunteers

Secondary objectives

To determine the effect of age in the effectiveness of countermeasures (blue light and coffee)

To determine individual differences (cognitive, genetic and hormonal) in the impairment of neurobehavioral functions from sleep loss and in the effectiveness of countermeasures (blue light and coffee)

To determine the effects of blue light on quality and quantity of sleep after night-time driving in young and middle-aged healthy volunteers

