**Selection of participants**

Inclusion criteria

- Healthy volunteers
- Aged between 20-25 years or 40-50 years
- Male
- BMI between 18 and 27
- Moderate caffeine drinkers (2-3 cups by day)
- Non professional drivers had their driving license for at least 2 years and drove between 10000 and 20000 km per year
- Showing a morning or evening chronotype (Horne questionnaire score >58 or < 42 for young subjects and Horne questionnaire score >64 or < 53 for middle-aged subjects)

The patient’s informed consent must be obtained at the inclusion.

Exclusion criteria

- Evidence of psychopathology (self-reports symptom inventory SCL-90R score >59 on the general symptomatic index and the following symptom dimensions: depression, anxiety, paranoid ideation and psychoticism)
- Evidence of sleep disorders (Items of Basic Nordic Sleep Questionnaire >3),
- Evidence of excessive daytime sleepiness (Epworth sleepiness scale score >9)
- Hypopnea-apnea index ≥ 5 (assessed by polygraphy)
- Periodic leg movement index ≥ 15 (assessed by polygraphy)
- Sleep efficiency < 85 % (assessed by actimetry during 7 consecutive days)
- Shift-workers and jet-lag the month before their inclusion in the study
- Severe controlled or uncontrolled diseases (psychiatric disorders, neurological disorders, sleep disorders, hepatic or renal failure, unstabilized diabetes, neoplasic disorders, cardiovascular disorders, pulmonary disorders, digestive disorders,…)

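### The marker models in the protocol leave out age group, although the sample is built from two separated age groups, so an age difference could be reported as a cognitive or hormonal marker effect

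*Protocol*

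**What the plan says.** Under Selection of participants, entry is limited to men "Aged between 20-25 years or 40-50 years". Under Statistical considerations, the total of 48 is split as "24 young and 24 middle-aged". Age is therefore a two-level design factor, with a gap of at least 15 years between the groups.

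The secondary objectives treat age and markers as separate questions. One concerns the effect of age on how well the countermeasures work. Another is "To determine individual differences (cognitive, genetic and hormonal) in the impairment of neurobehavioral functions from sleep loss" and in the effectiveness of the countermeasures.

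The section Analyses of variables states the models:

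- For inappropriate line crossings (ILC), a negative binomial regression clustered on participants, "using number of ILC per participant as dependent variables and treatments (Blue light, coffee, or placebo), age or type as" determinants. Age and type are alternatives.
- For the standard deviation of lateral position, a two-way ANOVA listed as "age*treatment, genotype*treatment, hormonal type *treatment, cognitive type*treatment" and so on.
- For sleepiness, fatigue and the sleep outcomes, three-way versions of the same list, with time added.

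No section adjusts or stratifies a marker analysis for age, or says how cognitive or hormonal type is formed. Criteria of assessment lists the underlying measures as reaction times, error percentages and saliva concentrations, with no age norm.

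**The concern.** A two-way marker-by-treatment ANOVA has no place for a third factor, and neither does a three-way one whose other two factors are time and treatment. The known structure of the sample is therefore left out of exactly those models that are meant to explain differences between individuals.

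The Background and Expected results sections aim to find markers of vulnerability to sleep loss and of response to the countermeasures. Suppose slower reaction times, or a different cortisol level, are simply more common in one age group, and that group also drives differently at night or responds differently to treatment. A marker model without age then cannot tell a slow cognitive type from membership of an age group. The protocol's separate age and marker objectives would be answered by partly the same contrast.

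**Working it through.** **The plan's own figure.** The inputs are "Effect size f = 0.3", "α err prob = 0.05" and "Power (1-β err prob) = 0.9", giving 48. The test family, number of measurements and correlation are not stated. A repeated-measures ANOVA with three measurements and correlation 0 needs 49 (power 0.897 at 48); with correlation 0.5 it needs 25-26. So 48 is attainable but not fixed by the stated inputs. Nothing below depends on this: only the 24 + 24 split is used.

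**Assumptions, none of which the protocol supplies.** A continuous marker has SD 1 within each age group and a mean difference of d SD between groups. Type is a median split of the pooled 48 men. The marker has no effect within age group. The outcome is a within-person treatment contrast with SD 1, and age shifts it by δ SD.

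**Step 1: share of the age effect passed to the marker.** The pooled median lies midway between the group means, so the fraction of the higher-scoring age group that falls in the high type is p = Φ(d/2). The spurious difference between types is δ × (2p − 1).

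| d | p | share 2p − 1 |
|---|---|---|
| 0 | 0.50 | 0% |
| 0.5 | 0.599 | 20% |
| 1.0 | 0.691 | 38% |
| 1.5 | 0.773 | 55% |

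On a ratio scale, an age-by-treatment ratio of 2.0 would appear as a type-by-treatment ratio of 2.0 raised to the share: 1.15, 1.30 and 1.46 for d = 0.5, 1.0 and 1.5.

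**Step 2: false-positive rate for a null marker, age omitted.** With 24 men per type, the spurious contrast δ(2p − 1) is tested against a standard error of √(v × 2/24), where v = 1 + δ²p(1 − p). For d = 1.0 and δ = 0.6:

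- contrast: 0.6 × 0.383 = 0.230
- v = 1 + 0.36 × 0.691 × 0.309 = 1.077
- standard error: √(1.077/12) = 0.300
- non-centrality: 0.767
- rejection by a two-sided 5% t-test on 46 degrees of freedom: 11.7% (simulation: 11.6%)

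Across the range (the 0.2 and 0.3 columns by this approximation, the 0.6 and 1.0 columns by simulation):

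| d | δ = 0 | δ = 0.2 | δ = 0.3 | δ = 0.6 | δ = 1.0 |
|---|---|---|---|---|---|
| 0.5 | 5.0% | 5.2% | 5.5% | 7.0% | 9.2% |
| 1.0 | 5.0% | 5.8% | 6.7% | 11.6% | 22.1% |
| 1.5 | 5.0% | 6.6% | 8.6% | 19.7% | 41.0% |

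**Step 3: age group added.** In the simulated settings with δ = 0.6-1.0, rejection falls to 4.8-5.3% and the spurious contrast disappears.

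**Step 4: the ILC model type.** A clustered negative binomial model was simulated with an age incidence rate ratio (IRR) of 0.5 and a null marker, 600 runs per setting.

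| d | Marker IRR, age omitted | Rejected | Marker IRR, age included | Rejected |
|---|---|---|---|---|
| 1.0 | 0.78 | 17.5% | 1.00 | 7.5% |
| 1.5 | 0.69 | 30.5% | 0.99 | 9.7% |

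The IRRs without age agree with Step 1 (0.5 to the power 0.383 is 0.77; to the power 0.547, 0.68). Adjustment removes the bias, but some rejection above 5% remains with 48 clusters.

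**The case against.** Several counter-arguments have force.

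- **The protocol does not say that it expects an age difference.** A reader might infer this from the age objective, but that objective only sets out to determine an effect. Expected results predicts benefit, and equal benefit of blue light and coffee, in both age groups. Nor do the documents say that reaction time, cortisol or amylase differs by age. This stands: the bias is conditional on both associations.
- **The large error rates are one corner of the range.** With no age effect, or no age gap in the marker, there is no inflation; with small age effects there is little. This also stands. A flat statement that the marker tests exceed 5% would not be supported.
- **Type is undefined, and a statistical analysis plan could form types within age group.** That would largely remove the problem. The protocol does use age-specific cut-offs for chronotype under Selection of participants, and age-specific apnoea limits in the Polygraphy paragraph. But it does not extend this to cognitive or hormonal type. The models are written out, so this is more than an omitted detail. The alternative in the ILC sentence could loosely mean and/or, and the lists trail off. However, two-way and three-way models of the listed form still hold only one subject-level factor.
- **The ILC sentence names no interaction.** The type-by-treatment ratios in Step 1 therefore bear on the ANOVA outcomes, and on ILC only if that interaction is tested.
- **For pure prediction, an unadjusted marker may be what is wanted.** The Background speaks of identifying vulnerable drivers, and a marker that tracks age can do that. Expected results speaks of explaining variability, which calls for adjustment. Reporting both meets both aims.

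**Conclusion.** The point holds in conditional form. As written, every marker model omits the factor on which the sample was built, so a positive cognitive or hormonal finding could not be separated from an age-group difference. How much this matters depends on two associations that the protocol does not give. Under the assumed median split and normal contrast, the false-positive rate for a null marker lies anywhere from 5% to about 41%, and below 10% when the age effect is 0.3 SD or less.

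A reader might go further and infer that the main comparison of blue light, coffee and placebo is compromised. It is not: each man receives all three conditions, so age group cannot confound the overall treatment contrast. Nor do the documents give a reason to think that the genotypes differ by age group. The point concerns secondary marker analyses only. It is worth correcting because the remedy is simple and uses data that will be collected anyway.

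**What to change.** In Analyses of variables, name age group and type together in the ILC model instead of as alternatives. In each marker model, for ILC and for the secondary outcomes, keep age group as a factor, and add age group by treatment wherever type by treatment is tested. Report the age-adjusted marker effect as the result; show the unadjusted one beside it if prediction alone is of interest. Using the same form for genotype keeps the models consistent.

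The cost is a change of wording and no new data. Age group takes (2 − 1) = 1 degree of freedom, and age group by treatment takes (2 − 1) × (3 − 1) = 2. Estimates will be less precise for markers strongly tied to age, which reflects how little the sample can say about such markers apart from age. In the clustered negative binomial model the adjusted test may still reject somewhat too often, so borderline ILC marker results should be read with caution.

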**Study design**

Experimental design

This is an interventional study: Double-blind (except for blue-light), Randomized, Crossover, Comparative versus referent countermeasure of sleepiness: coffee (2*200 mg of caffeine) and placebo.

The study is divided into the following periods:

1. **selection period** without treatment between selection and inclusion visits to check the absence of exclusion criteria with questionnaires, polygraphic recording (respiratory sleep disorders and periodic leg movements) and actimetry (sleep efficiency, total sleep time)
2. **acute treatment period**, each volunteer will be randomly allocated to successively and randomly receive either continuous blue light exposure or 2*200 mg of caffeine or placebo of caffeine during night driving with at least 1 week between treatment.

Experimental protocol

SELECTION

Participant will complete the French version of the Basic Nordic Sleep Questionnaire (BNSQ), the self-report symptoms inventory SCL-90R, the chronotype questionnaire of Horne and Ostberg, the Epworth sleepiness scale. They will to have 7 consecutive days monitoring using actimeters and 1 night using polygraph.

INCLUSION

Participants will be screened for eligibility criteria. They will sign informed consent, perform cognitive tests, complete the caffeine sensitivity questionnaire. Blood samples will be collected.

DRIVING SESSION

Each subject, will come at the laboratory at 9:30 PM, and will kept awake until the time of the experimental session.

For each driving session (Blue light, caffeine and placebo of caffeine), all participants will drive 400 km (250 miles) on the same 2-lane highway for 4 hours. After 2 hours of driving (200 km, 125 miles) subjects will take a 15-minutes break. The night-time driving session will start at 1:00 AM and Stop at 5:15 AM. At the beginning, middle and end of the driving, participants will be asked to rate their instantaneous fatigue and sleepiness. After driving, sleep recuperation will be recorded in laboratory during a minimum of 6h. Saliva will be collected before and after the driving session and after sleep recuperation.

The subjects were instructed to maintain a regular sleep-wake schedule and were monitored by actimetry during the 3 days preceding each experimental session and during the 3 days after each experimental session.

**
[figure not shown]
**

C: Coffee

P: Placebo

BL: Blue Light

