**Criteria of assessment**

Primary efficacy criterion

- Number of inappropriate line crossings (ILC) identified from the video recordings.

Secondary efficacy criteria

- Standard deviation of the position of the car
- Self-rated sleepiness during driving
- Self-rated fatigue during driving
- Sleep latency during the subsequent sleep
- Sleep efficiency during the subsequent sleep
- Time course of EEG slow wave activity during the subsequent sleep

Secondary criteria

- Chronotype
- Caffeine sensitivity
- Habitual sleep patterns
- PER3 polymorphism
- COMT polymorphism
- ADORA2A polymorphism
- Reaction time and percentage of errors at cognitive tests
- Saliva cortisol concentration before and after the driving session and after the sleep recovery.
- Saliva amylase concentration before and after the driving session and after the sleep recovery.

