**Clinical assessment methods**

EFFICACY

Driving session

Driving conditions will be a straight highway on weekdays with usually light traffic conditions, in fair weather. All drivers will be exposed to the same or very similar conditions. During a training session, participants will be instructed to maintain a constant speed (130 kph [80 mph]), to drive in the center of the lane, and not to cross the painted lines separating the lanes except to pass a slower vehicle.

During the whole experiment, a professional driving instruc­tor will monitor the driving speed. He will be ready to take control of the car (equipped with dual controls) if needed. If a participant could no longer drive during a session, he will drive back to the rest area. The car used for the experiment will be equipped with a video system that calculates the driving ability.

The main outcome measure will be the number of inappropriate line crossings (ILC) identified from the video recordings. This measure was selected because epidemiologic findings have shown that 65% of sleep-related accidents occur after an ILC (Sagberg 1999). Several studies have also shown that impaired daytime alertness induces lateral devia­tions during driving (O'Hanlon and Volkerts 1986; Ramaekers and O'Hanlon 1994; O'Hanlon, Vermeeren et al. 1995) and that sleep-related accidents frequently occur with a single car driving off the road and hitting an obstacle with no reaction from the driver (Pack, Pack et al. 1995; Sagberg 1999). We have also demonstrated that the number of ILCs is affected by sleep deprivation (Philip, Sagaspe et al. 2005; Philip, Sagaspe et al. 2005) and improved by classic countermeasures to sleep loss (Philip, Taillard et al. 2006).

An ILC is recorded when the car cross a lateral highway lane marker, as evidenced by video-recording analysis. Exceptions are overtaking manoeuvres or some other necessary driving action, as recorded by the driving instructor. Driving-instructor and video-recording timelines were synchronized at the beginning of each ses­sion. Deviations related to traffic interference will be excluded so as to concentrate on line crossings related to driver status.

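### The primary model takes the raw number of line crossings with no exposure term, although the protocol foresees drives cut short because the participant can no longer drive; this can dilute the treatment ratios towards 1.

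*Protocol*

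**What the plan says.** All places are in the protocol; the statistical analysis plan is not at hand.

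- *Criteria of assessment*: the primary criterion is "Number of inappropriate line crossings (ILC) identified from the video recordings", a count and not a rate.
- *Analyses of variables*: the model is a negative binomial regression "using number of ILC per participant as dependent variables and treatments (Blue light, coffee, or placebo), age or type as" explanatory terms, with clustering by participant. Each man drives three sessions, so the count is read here as one per participant and session. Treatments are compared by incidence rate ratios, with a Wilcoxon test as fallback where there are no crossings. No offset, time or distance is mentioned for either.
- *Clinical assessment methods*, Driving session: the instructor may take control of the car, and "If a participant could no longer drive during a session, he will drive back to the rest area". No rule says how the crossings of such a session are counted. The same section instructs a constant speed of 130 km/h.
- *Study design*, Driving session: the plan for every session is that "all participants will drive 400 km (250 miles) on the same 2-lane highway for 4 hours". A pause of a quarter of an hour falls at the half-way point, and the clock runs from 1:00 to 5:15 AM.

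**The concern.** A ratio of counts is a ratio of rates only if the participants drive equally long under each treatment. The protocol describes an event that breaks this equality, and the event is not random: being unable to continue a drive between 1 and 5 AM is an extreme form of the impairment that line crossings are meant to measure. The drive stops adding crossings because the driver is doing badly.

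At stake are two results that the protocol expects: that both countermeasures beat placebo, and that blue light does as well as coffee. More stops under placebo would shrink the first contrast. Unequal stops under the two countermeasures would distort the second. The Wilcoxon fallback on raw counts has the same weakness.

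**Working it through.** **1. Planned exposure.** Inputs from *Study design*: 1:00 to 5:15 AM is 4.25 h; less the 0.25 h break, 4.0 h. 400 km / 4 h = 100 km/h. That section agrees with itself. Against the instructed 130 km/h it does not hold:
- 130 × 4 = 520 km, which is 30% more than 400 km;
- 400 / 130 = 3.08 h (about 3 h 05 min), which is 23% less than 4 h.

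If the actual length L is the same in every session, it cancels: (rate on treatment × L) / (rate on placebo × L) is the rate ratio. The mismatch alone therefore does not bias the treatment comparison.

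**2. A single stopped session.** Expected count = rate × hours driven. With assumed rates, a driver at 2 ILC/h who stops after 1 h scores 2, and a driver at 1 ILC/h who completes 4 h scores 4. The count ratio is 0.50 and the rate ratio 2.0. In general a driver with R times the rate scores lower once he stops before 4/R hours (2 h for R = 2).

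**3. Treatment level.** The protocol gives no stop or crossing rates, so all inputs here are assumptions. Let a share p of placebo sessions stop half-way, in participants with k times the mean rate, with no stops on active treatment and a constant rate within a drive.

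Retained placebo count = 1 − p × k × 0.5; apparent IRR = true IRR / retained count.

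| p | k | Retained | True 0.50 reads |
|---|---|---|---|
| 2% | 2 | 0.98 | 0.51 |
| 5% | 2 | 0.95 | 0.53 |
| 10% | 2 | 0.90 | 0.56 |
| 20% | 3 | 0.70 | 0.71 |

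**4. What reversal would need.** In the last row a true 0.75 reads 0.75 / 0.70 = 1.07. This requires that the same men, at three times the mean rate, never stop when treated. If 10% of active sessions also stop, the active count retained is 1 − 0.10 × 3 × 0.5 = 0.85, and the ratio reads 0.75 × 0.85 / 0.70 = 0.91. Seen the other way, with a true ratio of 2 for the sleepier treatment and stops at 1 h, the raw ratio is 2 × (1 − 0.75p). It falls below 1 only if p exceeds two thirds.

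**5. What an offset recovers.** For the 10% row, total placebo time is 1 − 0.10 × 0.5 = 0.95 of plan. Count over time is 0.90 / 0.95 = 0.947, and 0.50 / 0.947 = 0.53. The offset moves 0.56 to 0.53, not to 0.50, because the men with the highest rates contribute least time.

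A simulation with a rising rate shows the same. Assumptions: hourly rates in the ratio 1:2:3:4, 10 crossings per full placebo drive, gamma variation between participants with shape 1, and a stop after any hour with 6 or more crossings. About 20% of placebo and 5.5% of active sessions stop. A true 0.50 reads 0.64 on raw counts and 0.60 per time driven. The result depends on the setting: with shape 10 the raw figure is 0.54, and with a stop threshold of 10 crossings it is 0.55 (shape 1) or 0.51 (shape 4).

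**The case against.** The strongest reply is that this is an omission which a statistical analysis plan would fill. The paragraph is short, it does not say that shortened drives enter as raw counts, and reporting incidence rate ratios is compatible with an exposure term. In part this stands: the detailed handling of stopped sessions could be left to that plan. But the protocol itself names the dependent variable, the determinants and the effect measure. Followed as written, it gives a ratio of truncated counts.

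The second reply is that stops may be rare. The participants are healthy men screened for sleep disorders, each is his own control, and at 2% stops the shift from 0.50 to 0.51 is negligible. This stands as a limit on the size. Balanced stopping would also give less bias.

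The third reply is that an offset does little by itself. This also stands, and is why the fix does not end with the offset.

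A reader might also infer that the conflict between 400 km, 4 h and 130 km/h biases the primary result. It does not if the actual length is common to all sessions; it is a separate inconsistency.

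**Conclusion.** The concern holds as a risk of dilution of unknown size. It rests on two things in the protocol: a primary model for a raw count with no exposure term, and a foreseen early end of the drive that depends on the outcome. The direction, towards 1 against placebo, depends on the assumption that stops are commoner under placebo. With half-way stops at twice the mean rate on placebo only, a true 0.50 reads 0.51 to 0.56 for 2% to 10% stops.

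A reader might go further and infer that the sleepiest drives will score as the safest, so that a treatment effect could be reversed. That is possible for a single session. For the comparison of treatments it needs extreme assumptions (step 4), and nothing in the protocol supports them.

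**What to change.** 1. Add log(time driven by the participant himself) as an offset in the negative binomial model, leaving out any time under instructor control. Use the corresponding rate in the Wilcoxon fallback. The synchronised video and instructor timelines should give driving time. Distance would serve as well if it is recorded, but the protocol does not say that it is.
2. Because the stop is informative, pre-specify a sensitivity analysis that counts a session stopped for inability to drive as unfavourable, for example by giving it that participant's worst rank among his three sessions. Report the number of stops per treatment.
3. Separately, reconcile *Study design* with *Clinical assessment methods* on 400 km, 4 h and 130 km/h, so that the planned exposure is defined. Which of them gives way is for the sponsor to decide.

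The cost is one extra variable, one extra analysis and a few sentences of text. The clinical rule for ending a drive is not affected.

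### The models named for this three-session crossover contain no session (period) term; adding one is a nearly free gain in precision, not the repair of a bias

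*Protocol*

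**What the plan says.** Under Study design, the protocol describes the trial as "Randomized, Crossover, Comparative versus referent countermeasure of sleepiness" and says that "each volunteer will be randomly allocated to successively and randomly receive either continuous blue light exposure or 2*200 mg of caffeine or placebo", "with at least 1 week between treatment". In each session "all participants will drive 400 km (250 miles) on the same 2-lane highway for 4 hours". Recovery sleep is recorded in the laboratory after every drive.

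Under Analyses of variables, the primary model is a negative binomial regression "using number of ILC per participant as dependent variables and treatments (Blue light, coffee, or placebo), age or type as" determinants, clustered on participant. The position-variability outcome gets a two-way ANOVA crossing treatment with age, genotype or another type. The ratings and the sleep outcomes get three-way repeated-measures ANOVAs that add time.

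Under Clinical assessment methods there is some preparation: "During a training session, participants will be instructed to maintain a constant speed". The route, car and length of that training are not stated.

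**The concern.** In a crossover, the session in which a condition is given is a factor that the design itself creates. Here there are plausible reasons for the outcome to change over sessions whatever the treatment. The same road is driven at the same hours three times. The first recovery sleep may also be disturbed by the unfamiliar laboratory, and the text describes no adaptation night there.

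The protocol does not leave the model open. It names the model family, outcome, determinants and clustering, so an analysis plan that followed this text literally would carry the omission forward. Clustering on participant deals with the correlation of repeated counts; it does not remove a difference between sessions. At stake is precision in a trial sized to detect a slight difference between coffee and blue light.

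**Working it through.** **1. Terms named in each model**

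| Outcome | Factors named | Session number? |
|---|---|---|
| Line crossings (primary) | Treatment, age or type; clustered on participant | No |
| Position variability | Treatment by age, genotype, hormonal or cognitive type; list left open | Not named |
| Sleepiness, fatigue | Same, plus time; list left open | Not named; ratings are taken at the start, middle and end of a drive |
| Sleep latency, efficiency, EEG power | Same, plus time; list left open | Not named; time is not defined for latency and efficiency |

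**2. The plan's own figure.** "Total sample size: 48" is reproduced by a one-way ANOVA with three conditions, f = 0.3, alpha 0.05 and power 0.90. This needs 144 observations (noncentrality 0.09 × 144 = 12.96), and 144/3 = 48 participants. The protocol does not state the test family, so this route is inferred. A session term does not change the 48.

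**3. Chance imbalance in session position.** Assume each participant's order is drawn independently from the six possible orders. The difference in position between two treatments is ±1 with probability 2/3 and ±2 with probability 1/3. Its mean is 0 and its variance is (2/3)·1 + (1/3)·4 = 2. With 48 participants the mean difference has SD √(2/48) = 0.204 session, so the 95% range is ±1.96 × 0.204 = ±0.40 session. For an assumed fall per session, the rate ratio could be shifted by a factor of up to exp(0.40 × |ln(1 − fall)|):

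- 10% fall: exp(0.40 × 0.105) = 1.04
- 20% fall: exp(0.40 × 0.223) = 1.09
- 30% fall: exp(0.40 × 0.357) = 1.15

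**4. How much of the sampling error this is.** The shift is part of the ordinary sampling error of the log rate ratio, not an addition to it. A simulation with 48 participants, mean count 5 and dispersion 1 (all assumed; 3000 runs) gave:

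| Assumed fall per session | SD without session term | SD with session term | Reduction |
|---|---|---|---|
| 20% | 0.216 | 0.208 | 1 − 0.208/0.216 = 4% |
| 30% | 0.228 | 0.210 | 1 − 0.210/0.228 = 8% |

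With no session effect the term had no measurable cost. The 95% sampling factor without the term is exp(1.96 × 0.216) = 1.53 to exp(1.96 × 0.228) = 1.56, far wider than the imbalance alone.

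As a cross-check, subtract only the imbalance variance from step 3:

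- 20% fall: √(0.216² − (0.204 × 0.223)²) = 0.211, a 2% reduction
- 30% fall: √(0.228² − (0.204 × 0.357)²) = 0.216, a 5% reduction

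The order of magnitude agrees. The exact figure depends on the assumed variance structure.

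**5. Bias, type I error and power.** A linear model served as a stand-in for the clustered negative binomial: 48 participants, within-participant SD 1, treatment difference 0 or 0.6 SD, 3000 runs per setting. The learning effects are assumed.

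| Learning per session (SD) | 0 | 0.25 | 0.5 | 1.0 |
|---|---|---|---|---|
| Random orders, no term: type I error | 5.0% | 4.9% | 5.0% | 5.3% |
| Random orders, no term: power | 83% | 82% | 75% | 53% |
| Random orders, with term: power | 83% | 83% | 81% | 83% |
| Balanced orders, no term: type I error | 4.1% | 4.3% | 2.3% | 0.5% |
| Balanced orders, no term: power | 84% | 82% | 76% | 55% |
| Balanced orders, with term: power | 83% | 83% | 84% | 81% |

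The average estimate without the term stayed within 0.01 of the truth in every setting. Balance alone does not recover the power, because the session effect still inflates the estimated error. The term recovers it under either allocation.

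**The case against.** Three stronger readings are tempting, and the document does not support them.

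- **That learning biases the treatment comparison.** Order is randomised. The mean estimate is right and type I error is nominal under random orders, even with large learning.
- **That orders are not balanced.** The text states no balancing method, but the design figure is not available and may show the orders. Simple randomisation is not stated either. If orders are balanced and sessions complete, the shifts in step 3 vanish.
- **That a shift of 9% to 15% is an error on top of the confidence interval.** It is already inside the sampling error; the reduction in SD is the proper measure.

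It can also be argued that learning will be small. There is a training session, the road is straight, and participants must have held a licence for at least two years and drive 10,000 to 20,000 km a year. This is a fair point: no learning rate is given, and at a 10% fall per session even an extreme imbalance moves the ratio by only about 4%. The training may do little, however, for a first-night effect on laboratory sleep.

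Finally, the ANOVA lists are left open, and a separate analysis plan could add the term without contradicting the protocol. That limits the weight of the point. It does not remove it for the primary model, whose determinants are listed without session.

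**Conclusion.** The point holds as a missing precision term. The primary model and the listed secondary models name no session factor, although the design has three sessions per participant. The treatment comparison remains valid on average. The loss is about 4% to 8% in the SD of the log rate ratio under an assumed 20% to 30% fall in crossings per session. It is less for smaller effects and nil if there is no session effect. In the linear stand-in, power falls appreciably only when learning reaches about half a within-participant SD per session. All of these sizes rest on assumed session effects, counts and dispersion, because the protocol gives none. The need for the term does not depend on how orders are allocated, since balanced orders without it give a conservative test and a similar loss of power.

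**What to change.** Add session number (1, 2, 3) as a categorical factor to the negative binomial model, and report the treatment rate ratios adjusted for it. Add the same factor to the models for the secondary outcomes. For the repeated-measures analyses a linear mixed model carries it most easily, because session varies within participant alongside treatment. State what time means for each sleep outcome.

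State the order scheme in the text. If the design figure does not already show balanced orders, allocating the six orders equally within each age group is a reasonable optional complement: 24/6 = 4 participants per order in each group, 48/6 = 8 overall.

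The cost is two degrees of freedom and, if adopted, a randomisation list stratified by age group. The sample size and the burden on participants do not change.
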